**Methods and analysis:**

BOOSTB4 is an exploratory, open-label, multiple dose, phase I/II clinical trial evaluating safety and efficacy of postnatal (n=15) or prenatal and postnatal (n=3, originally n=15) administration of BOOST cells for the treatment of severe OI compared with a combination of historical (1–5/subject) and untreated prospective controls (≤30). Infants<18 months of age (originally<12 months) and singleton pregnant women whose fetus has severe OI with confirmed glycine substitution in *COL1A1* or *COL1A2* can be included in the trial.

Each subject receives four intravenous doses of 3×10^6^/kg BOOST cells at 4 month intervals, with 48 (doses 1–2) or 24 (doses 3–4) hours in-patient follow-up, primary follow-up at 6 and 12 months after the last dose and long-term follow-up yearly until 10 years after the first dose. Prenatal subjects receive the first dose via ultrasound-guided injection into the umbilical vein within the fetal liver (16+0 to 35+6 weeks), and three doses postnatally.

The primary outcome measures are safety and tolerability of repeated BOOST cell administration. The secondary outcome measures are number of fractures from baseline to primary and long-term follow-up, growth, change in bone mineral density, clinical OI status and biochemical bone turnover.

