Parent’s/legal guardian’s signed informed-consent form Clinical diagnosis of OI type 3 or severe 4 *AND* Molecular diagnosis of OI (glycine substitution in the collagen triple-helix encoding region of either the *COL1A1* or *COL1A2* gene) Age less than 18 months¶ (calculated from gestational week 40+0, ie, the corrected age) Parent/legal guardian over 18 years of age	Woman has signed the patient consent form Only women where termination of the pregnancy is no longer possible or where the women are committed to continue the pregnancy may be included in the trial Suspicion of OI type 3 or severe 4 in the fetus on ultrasound findings *AND* Molecular diagnosis of OI in the fetus (glycine substitution in the collagen triple-helix encoding region of either the *COL1A1* or *COL1A2* gene) Gestation age between 16+0 and 35+6 weeks+days Pregnant women over 18 years of age	*Matched historical controls (1-5/subject):* Parent’s/legal guardian’s signed informed-consent form Clinical and molecular diagnosis of OI (glycine substitution in the collagen triple-helix encoding region of either the *COL1A1* or *COL1A2* gene) Data on fractures and growth are available Parent/legal guardian over 18 years of age *Prospective untreated controls (n=up to 30):* Postnatal participation: the inclusion criteria for the postnatal group apply Prenatal participation: the inclusion criteria for the prenatal group apply, except inclusion criteria 2

Exclusion criteria		
Postnatal group (n=15)	Prenatal group (n=3)§	Control group (n=18–120)

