Existence of other known disorder that might interfere with the treatment, such as, but not limited to organ disfunction (eg, liver or renal failure or bronchopulmonary dysplasia), congenital heart defect, hypoxic encephalopathy l–lll, severe neurological problems, immune deficiencies, muscle diseases, severe malformations or syndromes diagnosed by clinical examination Any contraindication for invasive procedures such as a moderate/severe bleeding tendency Known risk factors for clotting, such as, but not limited to previous blood clot, family history of clots, clotting disorder (inherited or acquired), heart failure, inflammatory disorders (eg, lupus, rheumatoid arthritis, inflammatory bowel disease) Positive Donor Specific Antibody-test Known allergy/hypersensitivity to Fungizone and/or Gensumycin Abnormal karyotype or other confirmed genetic syndromes Oncologic disease (previous or current malignancy) Inability to comply with the trial protocol and follow-up schedule Inability to understand the information and to provide informed consent	Multiple pregnancy Coexistence of other disorder that might interfere with the treatment, as judged by the Investigator or the patient’s obstetrician Abnormal fetal karyotype or other confirmed genetic syndrome Any contraindication for invasive procedures such as a bleeding tendency or contagious infections, such as, but not limited to HIV, syphilis, hepatitis B, hepatitis C or other known infectious diseases that can harm the fetus Known risk factors for clotting, such as, but not limited to previous blood clot, family history of clots, clotting disorder (inherited or acquired), heart failure, inflammatory disorders (eg, lupus, rheumatoid arthritis, inflammatory bowel disease) Positive Donor Specific Antibody-test Known allergy/hypersensitivity to Fungizone and/or Gensumycin Oncologic disease in woman or fetus (previous or current malignancy) Unwilling to or cannot undergo delivery by Caesarean section Inability to comply with the trial protocol and follow-up schedule Inability to understand the information and to provide informed consent	*Matched historical controls (1-5/subject):* Existence of other disorder that might interfere with the trial. No lung hypoplasia (type 2 OI) Abnormal karyotype *Prospective untreated controls (n=up to 30):* Postnatal participation: the exclusion criteria, except exclusion criterium 2, 3, 4 and 5 (contraindication for invasive procedure, known risk factor for clotting, Positive Donor Specific Antibody-test and Known allergy/hypersensitivity to Fungizone and/or Gensumycin) for the postnatal group apply Prenatal participation: the exclusion criteria, except exclusion criterium 1, 4, 5, 6 and 7 (multiple pregnancy, contraindication for invasive procedure, known risk factor for clotting, Positive Donor Specific Antibody-test and Known allergy/hypersensitivity to Fungizone and/or Gensumycin) for the prenatal group apply

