### Sample size calculation

No formal power calculations has been performed. OI is a rare disease, and a limited number of subjects can be included each year. Based on the incidence, it was originally reasonable to include 30 patients (15 postnatal subjects and 15 prenatal subjects) in this first trial on the grounds of feasibility, suitable time period and for the application of descriptive statistical analyses. However, in an amendment to the original protocol in 2023, which is approved by the Competent Authorities, the number of subjects in the prenatal group was reduced from 15 to three. This change was requested by the Sponsor due to time restrictions in the academic funding of the trial. The risk‒benefit balance for participation in any of the trial groups was not changed. Since the purpose of the prenatal trial group was to demonstrate feasibility of administration of one dose of BOOST cells before birth and three doses after birth, this change to the original protocol is not considered to alter the outcome of the trial’s objectives.

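### Table 1 exempts prenatal prospective controls from the singleton and continuing-pregnancy rules that every treated prenatal pregnancy must meet, so birth, growth and fetal-outcome comparisons may not be like-for-like

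*Protocol article*

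**What the plan says.** All references are to the protocol article.

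- **Treated prenatal group (Table 1).** The second inclusion item reads: "Only women where termination of the pregnancy is no longer possible or where the women are committed to continue the pregnancy may be included". The first exclusion item is multiple pregnancy. Every treated pregnancy must satisfy both.
- **Prospective controls enrolled prenatally (Table 1).** For inclusion, "the inclusion criteria for the prenatal group apply, except inclusion criteria 2". For exclusion, the waiver begins: "Prenatal participation: the exclusion criteria, except exclusion criterium 1, 4, 5, 6 and 7 (multiple pregnancy". The other waived exclusions are contraindication to invasive procedures, clotting risk, donor-specific antibodies and allergy to two named agents.
- **Abstract, Methods and analysis.** The population is given as "singleton pregnant women whose fetus has severe OI".
- **Matching (Table 2).** OI type and age at start of bisphosphonate are required. Sex, identical variant and time of diagnosis are used only if more than five controls are available. Plurality is not listed.
- **Endpoints (Outcome measures).** Growth and, for the prenatal group, fractures present at birth are secondary endpoints. Fetal adverse events, morbidity and mortality fall within the safety focus.
- **Size (Sample size calculation).** By amendment, "the number of subjects in the prenatal group was reduced from 15 to three". Up to 30 prospective controls are allowed, with no split between prenatal and postnatal entry.

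**The concern.** Most of the waived exclusions concern the safety of giving the cells, so dropping them for untreated controls makes sense. The singleton and continuing-pregnancy rules are different, because they bear on the outcomes being compared.

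**Plurality.** If twins are smaller at birth than singletons (a general assumption; the documents give no figure), a twin control lowers control birth size and early growth. The treated children then look better for a reason unrelated to treatment. Plurality may also affect fractures at birth, in a direction the documents do not settle.

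**Continuation.** A treated woman has passed the point of decision, or has committed to continue, before she enters. A control may decide after entry. Elective terminations can then appear among control pregnancies with almost no treated counterpart. If they were tabulated with fetal losses, the control fetal outcome would look worse and treatment safer.

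**Working it through.** **1. Which rules are waived.** The list numbers did not survive extraction, so criterion 2 has to be identified by order. The exclusion waiver gives numbers and labels together: 1 multiple pregnancy, 4 invasive-procedure contraindication, 5 clotting risk, 6 donor-specific antibodies, 7 allergy. These match the order of the prenatal exclusion list exactly. Reading the inclusion list the same way makes item 2 the continuing-pregnancy rule.

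**2. Stated counts.** Treated: 15 + 3 = 18. Historical controls: 18 × 1 = 18 to 18 × 5 = 90. Maximum control group: 90 + 30 = 120. These reproduce the 18–90 in Statistical analysis and the 18–120 in Table 1. No count is in dispute.

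**3. How likely a multiple pregnancy is among controls.** The documents give neither a multiple-pregnancy rate nor the number m of prenatal controls, so both are assumed. P(at least one) = 1 − (1 − p)^m.

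| m | p = 1% | p = 5% |
|---|---|---|
| 3 | 3% | 14% |
| 10 | 10% | 40% |
| 30 | 26% | 79% |

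The expected number of multiple pregnancies is m × p: 0.1 to 0.5 for m = 10, and 0.3 to 1.5 for m = 30.

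**4. Weight of one twin control.** Suppose one prospective twin child joins a treated subject's historical controls, of whom there are one to five. Its share of that set's mean is 1/(1 + 1) = 50% down to 1/(5 + 1) = 17%. With three treated prenatal subjects there are only three such sets.

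**5. Does the continuation waiver change the severity mix of live-born children?** Let severity s be standard normal, with termination probability 1/(1 + exp(−(a + b·s))). All values are assumed, with 2,000,000 simulated fetuses per run. Termination precedes enrolment in the treated group and may follow it in controls.

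With the same propensity in both groups (a = 0, 50% terminated), mean severity among the live-born, in SD, is:

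| b | treated | control |
|---|---|---|
| 0 | 0.00 | 0.00 |
| 0.5 | −0.24 | −0.24 |
| 1 | −0.41 | −0.41 |
| 1.5 | −0.53 | −0.53 |

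The timing of the decision makes no difference. A gap appears only if the propensity itself differs. At b = 1, with 30% terminated in the treated source population and 50% among controls, the means are −0.255 and −0.412, so treated children are 0.16 SD more severe. With 40% against 50% the gap is 0.08 SD. The documents give no basis for assuming such a difference.

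**6. Can a terminated control enter the matched comparison of children?** All controls are to receive bisphosphonate, and age at its start is a required matching factor. A terminated pregnancy can meet neither condition. The matching rules therefore already keep terminations out of the postnatal comparison. They do not govern a count of fetal outcomes from enrolment.

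**The case against.** The best defence has four parts.

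- **Scope.** Three treated fetuses are involved, the Sample size calculation section gives the prenatal group's purpose as feasibility, no power calculation was made, and the analysis is descriptive with each child as its own control. This stands, and it limits the point to a minor one.
- **The abstract.** Its singleton wording can be read as describing treated pregnancies only, with controls mentioned separately. That is a fair reading. At most the abstract is an imprecise summary of an explicit exemption in Table 1.
- **Plurality elsewhere.** Neither the postnatal group nor the historical controls have a plurality criterion. This also stands. Even so, all treated prenatal pregnancies are singleton, and the prospective controls are the ones for whom the rule was expressly lifted.
- **Tabulation of terminations.** The primary endpoint is administration-related events, and no treated-versus-control test of fetal loss is described. How terminations are tabulated could be left to the full protocol or analysis plan. This is partly right. However, the unequal entry rule is stated in the article, and the trial is described as evaluating safety as well as efficacy against controls, with all reported adverse events analysed whatever their cause and the fetus analysed separately.

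**Conclusion.** The point holds in a narrow form. Prenatal prospective controls enter under looser rules than the treated prenatal group on two features that bear on outcome. Plurality is not restored by matching, so one twin control could visibly move a small matched set. The chance of this depends on two figures the documents do not give. Elective termination after enrolment is possible essentially only in controls. A treated woman who committed to continue could still change her mind, so the contrast is not absolute. A fetal comparison counted from enrolment therefore does not set like against like.

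A reader might infer more: that live-born controls become a milder, self-selected group and the fracture comparison is biased against treatment. The documents do not support that. Live-born treated children also come only from continued pregnancies, and the waiver merely moves the decision from before entry to after it. Bias would need a different severity-related propensity to terminate in the two groups, for which there is no evidence here. A reader might also infer that terminated controls use up scarce places. The 30 is a ceiling, not a quota, and nothing shows that places are short.

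The 15 postnatal subjects are not affected. This is a minor but cheap improvement.

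**What to change.** Keep the waiver for enrolment if the sponsor wants it. Add to Tables 1 and 2 that a prospective prenatal control is matched to a prenatally treated subject only if the pregnancy is singleton and met prenatal inclusion criterion 2. Count fetal follow-up in controls from the date that criterion was met, and list elective terminations separately from fetal losses. Bring the abstract into line by saying whether its singleton wording covers controls.

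The cost is a few lines of text and two recorded items per prenatal control: plurality, and the date on which continuation was settled. That date may have to be recovered for controls already enrolled. A few prenatal controls may drop out of an already small descriptive comparison. Long-term follow-up runs to 2032, so the rule can still be applied to it.

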### Sample size calculation

No formal power calculations has been performed. OI is a rare disease, and a limited number of subjects can be included each year. Based on the incidence, it was originally reasonable to include 30 patients (15 postnatal subjects and 15 prenatal subjects) in this first trial on the grounds of feasibility, suitable time period and for the application of descriptive statistical analyses. However, in an amendment to the original protocol in 2023, which is approved by the Competent Authorities, the number of subjects in the prenatal group was reduced from 15 to three. This change was requested by the Sponsor due to time restrictions in the academic funding of the trial. The risk‒benefit balance for participation in any of the trial groups was not changed. Since the purpose of the prenatal trial group was to demonstrate feasibility of administration of one dose of BOOST cells before birth and three doses after birth, this change to the original protocol is not considered to alter the outcome of the trial’s objectives.

### Blinding, intervention and follow-up

It would not be ethically appropriate to perform a randomised double-blind placebo-control trial in this population, particularly regarding the risks of the prenatal infusion procedure and the vulnerability of the subjects. No blinding or randomisation will therefore take place.

Four intravenous doses of BOOST cells are administered at 4 month intervals (range 3–5 months), please see figure 1 for an overview of the trial. For postnatal subjects, the first dose must be administered before 18 months of age (in the original protocol, it was before 12 months of age; an amendment that has been approved by the Competent Authorities). For prenatal subjects, the first dose will be given in utero during gestational weeks+days 16+0–35+6 via ultrasound-guided injection into the umbilical vein within the fetal liver, and the final three doses are administered postnatally. Each dose contains 3×10^6^ allogeneic expanded human fetal liver MSCs per kg bodyweight. All doses to a subject will be derived from one donor. No preconditioning or medicines after the administration will be administered.

**Figure 1 F1:**
[figure not shown]
Overview of the trial schedule. The BOOSTB4 trial consists of two parts; part 1 that includes information, consent, screening and inclusion. This is followed by four doses of BOOST cells at 4±1 month intervals with immediate in-patient follow-up over 48 hours after doses 1‒2, and over 24 hours after doses 3‒4 (48 hours for doses 1‒3 in the prenatal group). Part 1 of the trial also includes the primary follow-up at 6 and 12 months after the fourth and last dose. Part 2 of the trial consists of yearly long-term follow-up over 8 years until 10 years after the first dose. BOOST, Boost Brittle Bones Before Birth.

In-patient follow-up is performed over 48 (doses 1–2) or 24 (doses 3–4) hours in the postnatal group and over 48 (doses 1–3) or 24 (dose 4) hours in the prenatal group after each dose. Primary follow-up is performed at 6 and 12 months after the last dose, and long-term follow-up is performed yearly until 10 years after the first dose. At each visit and follow-up, AEs and parameters related to efficacy outcomes are recorded. Women in the prenatal group are followed under the same schedule.

Prospective controls will be subject to the same follow-up routine as the patients enrolled in the treatment group, as described above, with the option to opt in or out from blood collection. The clinical evaluation programme for the historical control group will be based on data available from the routine follow-up of OI patients in the respective country. The controls will be individually matched to each subject (see table 2). Between one and five historical controls will be included per subject and up to 30 prospective controls in total.

**Table 2 T2:** Matching of the controls

Matching of the controls	
The controls historical and untreated prospective will be individually matched to each trial subject:	
Type of OI*:	Type 3 with type 3. Severe type 4 with severe type 4.
Age at onset of bisphosphonate therapy:	Start of bisphosphonate treatment in the first 2 months of life. Start of bisphosphonate treatment from 2 to 12 months of life.
If possible (if more than five controls have been identified), matching will also be made on:	
Sex	
Identical OI pathogenic sequence variant	
Time for OI diagnosis	A control matched with a subject in the postnatal group was diagnosed† postnatally. A control matched with a subject in the prenatal group was diagnosed† prenatally.

One to five historical controls per subject and up to 30 prospective controls in total will be included and matched to each subject.

*No mixed OI types (eg, OI type 3/4, is allowed).

†Clinical diagnosis, molecular diagnosis not required at this time point.

OI, osteogenesis imperfecta.

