## Introduction

Osteogenesis imperfecta (OI) is a rare clinically and genetically heterogeneous group of heritable disorders of connective tissue characterised by osteopenia, growth restriction, bone deformities, fractures and chronic pain.^1^ Originally, OI was classified into four types according to clinical, radiological and histological findings, where type 1 refers to the mildest form, type 2 to the perinatally lethal form, type 3 to the most severe form compatible with life and type 4 to an intermediate group with moderate to severe types of OI.^2^ This classification covers 85%–90% of persons with OI and includes >1500 different autosomal dominant sequence variations in the genes coding for type I collagen (*COL1A1* or *COL1A2*).^1–3^ There is currently no curative treatment for OI, with the only available pharmaceutical treatments failing to address the underlying molecular pathology, the collagen defect.^4^ Treatment is aimed at increasing overall bone strength to prevent fractures and maintain mobility. Bisphosphonates are used to reduce bone resorption and increase bone mass.^5^ However, two meta-analyses of randomised trials on bisphosphonate treatment for OI did not demonstrate improvement in fracture rates, reduction of pain or improved functional mobility, although multiple studies report this independently.^6 7^

One child among 10–20 000 is born with OI. Diagnosis of severe types of OI is often made at the routine fetal anomaly ultrasound scan mid-pregnancy, or earlier if first trimester scanning is routine. Early treatment of OI is preferred to minimise irreversible pathology. Prenatal intervention offers multiple potential advantages over postnatal approaches; ameliorating and preventing damage that has begun already during fetal life, the relatively naive fetal immune system may permit the development of immune tolerance towards donor cells, infusion into the systemic fetal circulation may avoid sequestration of the cells in the lungs because circulatory shunts allow the pulmonary circulation to be bypassed, fetal life is a time of natural stem cell proliferation and migration to different anatomic compartments. Also, prenatal administration may enhance the effect of mesenchymal stem cells (MSCs) because there will be a lesser amount of poor quality OI type collagen that requires replacement, and finally, the possible psychological benefits for parents of commencing treatment as early in the child’s life.^8^

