### Trial status

Recruitment commenced in Sweden after the site opened on 12 August 2019. The first subject in the postnatal group was included and received the first dose on 17 March 2020. Due to the SARS-CoV-2 pandemic, only two subjects were included in the trial during 2020, and due to time restrictions for the project, the dose administrations are only performed at Karolinska University Hospital in Sweden. After a safety assessment by the Data and Safety Monitoring Board of at least one dose administered to the first five postnatal subjects in the trial, the prenatal group of the trial was opened on 17 June 2021, and the first prenatal dose was administered on 18 November 2021. By 2nd of March 2022, all 15 of 15 subjects in the postnatal group had been included and received their first dose, and by 14th of December 2021, three of 15 prenatal subjects had been included and administered with one prenatal dose each. No more subjects will be included in the prenatal group due to time restrictions in funding of the trial (an amendment approved by the Competent Authorities). The primary follow-up is currently being performed and is expected to be completed in January 2024, and the long-term follow-up will be completed in 2032.

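### Table 2 ties matching on time of OI diagnosis to the subject's trial group, not to the subject's own diagnosis, so prenatally detected children in the postnatal group would get discordant controls wherever that factor is used

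*Protocol article*

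**What the plan says.** Table 2 (Matching of the controls) has two tiers. Every control is matched on OI type and on age at start of bisphosphonate therapy. A second tier covers sex, identical sequence variant and time of OI diagnosis, and is conditional: "If possible (if more than five controls have been identified), matching will also be made on" these factors.

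The diagnosis-time row reads, for one group, "A control matched with a subject in the postnatal group was diagnosed† postnatally", and for the other, "A control matched with a subject in the prenatal group was diagnosed† prenatally". The footnote explains what counts as diagnosed: "Clinical diagnosis, molecular diagnosis not required at this time point". A fetus recognised clinically on ultrasound therefore counts as prenatally diagnosed, even if the molecular result came after birth.

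For the postnatal group, Table 1 asks for "Clinical diagnosis of OI type 3 or severe 4", a glycine substitution in *COL1A1* or *COL1A2*, and corrected age under 18 months. It does not say when the diagnosis must first have been made.

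**The concern.** A matching factor should make subject and control alike on that factor. The row is titled as time of diagnosis, but its rule never looks at when the subject was diagnosed; it looks at the group in which the subject was treated. The two agree for the prenatal group, whose entry criteria require ultrasound suspicion and a molecular diagnosis in the fetus. They need not agree for the postnatal group. A child seen on a prenatal scan but first treated after birth would be given postnatally diagnosed controls, while better-matched, prenatally diagnosed candidates are set aside.

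The trial is not randomised, and matching is the safeguard that the article describes for the comparison with controls. That comparison bears on fractures, the key secondary endpoint, and on growth. If skeletal signs visible before birth go with more severe disease within an OI type, the selected controls would be milder than the treated children.

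**Working it through.** **Planned control totals.** Treated subjects: 15 + 3 = 18. Historical controls at one to five each: 18 × 1 = 18 to 18 × 5 = 90. Adding up to 30 prospective controls gives a maximum of 90 + 30 = 120. These reproduce the 18–90 in Statistical analysis and the 18–120 in Table 1. Re-keying the diagnosis-time row changes none of them.

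**Can the postnatal group contain prenatally detected children?**

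- Eligibility: no criterion excludes them (Table 1).
- Frequency of detection: "Diagnosis of severe types of OI is often made at the routine fetal anomaly ultrasound scan mid-pregnancy" (Introduction). No percentage is given.
- Calendar (Trial status): "The first subject in the postnatal group was included and received the first dose on 17 March 2020", whereas "the prenatal group of the trial was opened on 17 June 2021". The gap is 15 months. The opening followed a safety assessment of the first five postnatal subjects, so at least 5 of the 15 entered when no prenatal group was open.
- Gestation limit: a pregnancy at 35+6 weeks on 17 June 2021 reaches 40+0 weeks 29 days later, on 16 July 2021. All 15 postnatal subjects had their first dose by 2 March 2022, about 7.5 months after that. A child with a corrected age above about 7.5 months on that date had no prenatal option, however early it was detected.

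Such children are therefore permitted and plausible, but not counted in the article.

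**How many could be affected?** Let q be the assumed share of the 15 postnatal-group children who were detected prenatally. The last two columns assume five controls per child and the factor applied to every child.

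| q | Expected children (15q) | Discordant pairs | Out of |
|---|---|---|---|
| 0.2 | 3 | 15 | 75 |
| 0.4 | 6 | 30 | 75 |
| 0.6 | 9 | 45 | 75 |

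The chance of at least one such child is 1 − (1 − q)^15: 79% at q = 0.1 and 96.5% at q = 0.2. Among the first five subjects alone, at q = 0.2, it is 1 − 0.8^5 = 67%.

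**Possible size of the distortion.** Let RR be the fracture-rate ratio, prenatally versus postnatally detected, that remains within the mandatory matching strata. The article does not give it; 1.2 to 2.0 is assumed. If the rule is applied to every postnatal-group subject, all controls are postnatally diagnosed, with relative rate 1. Without any treatment effect, the treated group has relative rate 1 + q(RR − 1). That is the factor by which the treated/control rate ratio is multiplied:

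- q = 0.2, RR = 1.2: 1 + 0.2 × 0.2 = 1.04
- q = 0.4, RR = 1.5: 1 + 0.4 × 0.5 = 1.20, so a true ratio of 0.80 would appear as 0.80 × 1.20 = 0.96
- q = 0.6, RR = 2.0: 1 + 0.6 × 1.0 = 1.60

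**Partial application.** Suppose the factor is used for only a fraction a of subjects, and that the remaining controls happen to have the same share q of prenatal detection as the treated children. The factor becomes [1 + q(RR − 1)] / [1 + (1 − a)q(RR − 1)]. With a = 0.5, q = 0.4 and RR = 1.5 this is 1.20 / 1.10 = 1.09, and a true 0.80 would appear as about 0.87.

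**Partial absorption.** If matching on OI type and bisphosphonate start reduces the remaining RR from 1.5 to 1.25, the full-application factor at q = 0.4 is 1 + 0.4 × 0.25 = 1.10.

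**The case against.** The strongest reply is that this is an optional, second-tier factor. A forced mismatch needs three things together: a prenatally detected child in the postnatal group, more than five candidates for that child after matching on type and bisphosphonate start, and a literal reading of the group label. OI is rare, and historical controls are promised only as far as possible, so the second condition may seldom be met. Below that number, diagnosis time is uncontrolled rather than reversed. This stands, and it limits the size of the problem.

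The mandatory factors may also carry part of the severity difference: mixed OI types are not allowed, and starting bisphosphonates in the first two months of life plausibly tracks early recognition. This stands too.

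The consequence is bounded. Safety is the primary endpoint, the efficacy analysis is descriptive, each subject also serves as his or her own control, and the article admits that it may be underpowered for efficacy. Under the assumed direction, the error would hide a benefit rather than create one.

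None of this defends the key itself. No feasibility reason favours trial group over the subject's own diagnosis time, since both are equally easy to apply once diagnosis time is known.

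Three stronger readings are tempting and not supported:

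- That prenatally detected children are in fact mispaired: the article reports neither how many there are nor how many candidates each subject has.
- That lack of Dutch approval for the prenatal part forced Dutch children into the postnatal group: dosing took place only in Sweden, and the article does not say that Dutch families were barred from prenatal inclusion there.
- That the more-than-five threshold, or the absence of a ranking of diagnosis time above sex, is an error: both are ordinary choices of feasibility or preference.

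**Conclusion.** The point holds in a limited form. Followed literally, the diagnosis-time row selects discordant controls for any prenatally detected postnatal-group child to whom it is applied. That such children may be present follows from the eligibility criteria, the Introduction and the trial dates; their number is unknown.

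The direction of bias, towards hiding a benefit on fractures and growth, rests on the assumption that prenatal detection marks more severe disease within a type. The factor of 1.20, and the wider range of 1.04 to 1.60 over the assumed inputs, are upper-end illustrations with the rule applied to all postnatal-group subjects. A reader might take them as estimates of the bias in this trial, which they are not: the article gives neither input and specifies no treated/control rate ratio. With partial application, or if the mandatory factors absorb part of the difference, the factor falls towards 1. The safety objective and the within-subject comparisons are unaffected.

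**What to change.** Reword the diagnosis-time row of Table 2 so that the control's time of clinical diagnosis, prenatal or postnatal, is the same as the subject's own. Keep it in the optional tier under the present condition. Record time of clinical diagnosis for every treated subject and every control. Add a sensitivity comparison of fractures and growth restricted to controls concordant with their subject on diagnosis time.

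The cost is one row of wording, one data item and one further analysis. The restricted comparison will have fewer controls and be less precise; the planned totals (18–90 historical, up to 120 overall) and the main analysis stay as they are. Long-term follow-up runs to 2032, so the correction can still serve that comparison.
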